## 1.2. Study Design Schematic

[figure not shown]

**Figure 1.** Diagram of the registry design for data collection

Note:

1. The study will retrospectively collect available data for patients who initiated DMT prior to recruitment initiation starting from index date. Index date will not be earlier than April 28th, 2019, which was the launch date of nusinersen, the first DMT in China. Baseline data will be collected within 30 days prior to the index date.
2. The index date for patients treated with any DMTs will be the date of DMT initiation, and the index date for those untreated patients will be the date of study enrollment.

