### 3.2.2. Available Therapies for Disease

Disease management is mainly based on a multidisciplinary management to improve motor, respiratory, gastrointestinal, and orthopedic symptoms. With technical advancements and thus the possibility to provide non-invasive ventilator support and enteral feeding to the affected patients, survival has increased. In 2017, a consensus statement for standards of care in SMA was published, nonetheless, there is high variability in the standards of care for patients with SMA.

Current therapeutic strategies include mainly respiratory, feeding and orthopedic management and supportive pharmacologic therapy. These therapies improve muscular function, quality of life and longevity, but do not directly target the disease mechanism. Presently in China, there is one registered and approved therapy to treat 5q-SMA patients (nusinersen). This compound is an antisense oligonucleotide targeting the splicing of exon 7 of the SMN2 gene, aiming at increasing the production of a full-length SMN protein. This compound is administered through intrathecal administration, with 4 loading doses over 63 days, followed by maintenance doses every 4 months. New therapeutic compounds, gene therapy (AVXS-101, Avexis) was approved by FDA and EMA recently. Small molecule targeting the splicing of SMN2 was also approved by FDA and EMA.

Based upon a better understanding of the molecular genetics of SMA, there has been a promising approach for the development of novel drugs intervening with the pathophysiology of SMA. Nusinersen is the first drug that has been approved for the treatment of 5q-SMA. It was approved in the United States in December 2016, in Europe in June 2017, and in China in February 2019.

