### **6.1. Inclusion Criteria**

To be eligible to participate in this study, candidates must meet the following eligibility criteria at Day 0, or at the time point specified in the individual eligibility criterion listed:

1. Ability of the participant and/or his/her legally authorized representative (e.g., parent or legal guardian), as appropriate and applicable, to understand the purpose and risks of the study, to provide informed consent, and to authorize the use of confidential health information in accordance with national and local privacy regulations.
2. Genetically confirmed 5q-SMA.
3. Age < 18 years at enrollment.

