This registry study will include both retrospective and prospective data collection. Eligible SMA patients will be recruited during the 24-month recruitment period and will be prospectively followed up to the end of study or deaths or willing to drop out, whichever comes first. If patients received DMT (including nusinersen and other DMTs) prior to the recruitment initiation and post April 28th, 2019 (as the date the first DMT, nusinersen, was launched in Chinese market), data will be retrospectively collected via medical chart review. Retrospective data collection will be considered complete for a participating patient if data of last available medical chart or latest survival status before recruitment initiation have been recorded in the electronic case report form (eCRF). Otherwise, patients will be prospectively followed up to the end of study or deaths or willing to drop-out, whichever comes first, after signing the ICF. For the DMTs treated group, the date of patients initiating DMT will be defined as the index date. For patients not receiving DMTs, the date of enrollment into the registry will be the index date. Baseline data will be collected within 30 days prior to the index date. Diagram of data collection is provided in Figure 1.

Since this is a non-interventional study and does not impose a visit schedule, patients will be treated according to physician's decisions. Only data that are available during routine visits will be documented. Recommended data collection schedules are set up to reflect the most likely patterns of routine clinical care of patients with and without DMT. To ensure the excellent level of compliance on data collection, schedule points are set to follow clinical routine visits, most likely happen on day 0, 14, 28, 63 then every 4 months for patients treated with nusinersen, and at day 0, 90 (in children with SMA type 1 < 2 years of age), 180 then every 6 months for untreated patients or those on other DMT. Retrospective data will be extracted according to the schedule as well.

CONFIDENTIAL

All data collected within the registry will be entered to the registry-specific e-forms by the responsible investigator, or a designated person, as timely as possible. Data entry and data corrections on e-forms are automatically tracked in the audit trail created by the EDC system. The EDC system and related IT infrastructure of this project will be based inside China.

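### The protocol gives conflicting index dates for an eligible child who started a DMT before 28 April 2019, so time zero and baseline are undefined for that child

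*Protocol*

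**What the plan says.** Section 1.2 (notes under the schematic) contains both rules.

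- Note 1 puts a calendar floor on the index date: "Index date will not be earlier than April 28", 2019. It gives the reason: "which was the launch date of nusinersen, the first DMT in China". It also fixes the baseline: "Baseline data will be collected within 30 days prior to the index date".
- Note 2 defines the index date by treatment start: "The index date for patients treated with any DMTs will be the date of DMT initiation". Untreated patients are indexed at enrollment.

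Section 9 repeats the initiation rule with no floor in that sentence: "For the DMTs treated group, the date of patients initiating DMT will be defined as the index date". It uses 28 April 2019 for another purpose, to describe whose data are collected retrospectively by chart review.

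Section 6.1 asks for consent, genetic confirmation of 5q-SMA, and "Age < 18 years at enrollment". Section 6.2 excludes only lack of consent and non-5q SMA. Neither mentions when or where a DMT was started. Section 9 asks sites to enroll eligible patients consecutively.

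Section 3.2.2 gives the approval history of nusinersen: "It was approved in the United States in December 2016, in Europe in June 2017, and in China in February 2019".

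**The concern.** All three approval dates in Section 3.2.2 precede the floor, so a start before 28 April 2019 is possible on the protocol's own facts, and nothing in the eligibility criteria keeps such a child out. For that child, one rule requires an index date before 28 April 2019 and the other forbids it.

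The index date decides what sites extract. Retrospective data begin at it (Section 1.2), the baseline window is counted back from it (Sections 1.2 and 9), and concomitant therapy is recorded from it (Section 7.2). If sites resolve the conflict differently, the inconsistency enters the eCRF, and an analysis plan can repair it only in part.

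If the floor is applied, the summaries most exposed are time to mortality, change from baseline, and safety early in treatment. For the affected children these would omit early response and early events, understate time on treatment, and use a baseline measured on treatment.

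**Working it through.** The protocol states no figure to reproduce here. The check is one of logic, followed by date arithmetic.

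**1. Consistency of the rules.** Let S be the date of the first DMT dose and I the index date.

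- Section 1.2 note 2 and Section 9: I = S.
- Section 1.2 note 1: I ≥ 28 April 2019.

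If S is on or after 28 April 2019, both hold. If S is earlier, they cannot both hold. No sentence gives one rule priority or says that an earlier start is moved to the floor.

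**2. Can S be earlier for an eligible child?** The criteria in Sections 6.1 and 6.2 contain no condition on S. The age limit applies at enrollment, with the first patient planned for Q3 2021 (Section 11.4), so it does not bar an earlier start. The gaps from the approval months in Section 3.2.2 to 28 April 2019, at 30.4375 days per month, are:

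| Approval | Days from last / first day of that month | Months |
|---|---|---|
| US, December 2016 | 848 / 878 | 27.9 / 28.8 |
| Europe, June 2017 | 667 / 696 | 21.9 / 22.9 |
| China, February 2019 | 59 / 86 | 1.9 / 2.8 |

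These are the longest gaps for a start after each approval. They show what was possible, not that any registry child was exposed.

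**3. If a site applies the floor (I = 28 April 2019).** Time zero is late by 28 April 2019 minus S: up to about 29 months for a start after US approval, and up to about 2 to 3 months for a start between Chinese approval and launch.

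The baseline window opens at 28 April 2019 − 30 days = 29 March 2019.

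- S before about 29 March 2019: the whole window falls after treatment start.
- S from then to 27 April 2019: part of the window falls after treatment start.

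**4. Illustration of prior exposure.** The nusinersen schedule described in Section 3.2.2 and the Synopsis is four loading doses ending on day 63 (63 / 30.4375 = 2.07 months), then one dose every 4 months.

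- Start 12 months before the floor: 4 + floor((12 − 2.07) / 4) = 4 + 2 = 6 doses.
- Start 24 months before the floor: 4 + floor((24 − 2.07) / 4) = 4 + 5 = 9 doses.

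A hypothetical child on that schedule would have had 6 or 9 doses by the assigned time zero.

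**5. If a site keeps the true start (I = S).** The 30-day window lies before treatment, so there is no on-treatment baseline. Note 1 is then breached.

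**6. Number affected.** The documents do not give it. Assumed shares of 0, 0.5, 1, 2 and 5% of about 600 patients (Section 11.5) give 0, 3, 6, 12 and 30 children.

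**The case against.** The strongest defence is that the floor is a statement of fact. It sits in the note on retrospective collection and gives commercial launch in China as its reason. The Synopsis describes treated patients as prescribed a DMT by their physician under local labelling, at sites in China. On that reading no start could be earlier, and the floor never takes effect. US and European approvals show availability abroad, not exposure among children seen at Chinese centers, and the interval between Chinese approval and launch is short. This stands as far as numbers go: the group may be very small or empty. It does not remove the conflict, because eligibility is not limited to commercial starts in China, and note 1 is worded as a limit on the index date.

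Section 9 might also be said to leave early starters out of retrospective collection. That is not secure. Section 9 speaks of patients who received a DMT after 28 April 2019, while Section 1.2 speaks of those who initiated one. A child who started in 2018 and continued dosing would fit the wording of Section 9.

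A reader might infer that early starters are certain to get a false time zero and an on-treatment baseline. The documents do not support that. Nothing resets an earlier start to the floor, and keeping the true start date is an equally available reading. Nor is enrollment a fallback index for these children, since the protocol assigns it only to untreated patients.

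Finally, handling in the analysis may belong to a statistical analysis plan that is not shown. That is fair for the summaries, but not for the index date, which the protocol itself defines and sites must apply when abstracting charts.

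**Conclusion.** The point holds as a contradiction in the definition of the index date for one subgroup: eligible children whose first DMT dose preceded 28 April 2019. Their index date, and with it their baseline window, cannot be derived from the protocol as written. A late time zero and an on-treatment baseline follow only if the floor is applied. Time zero would then be up to about 29 months late, with the baseline wholly on treatment for starts before about 29 March 2019.

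The reach is limited. The number of children is unknown; 0 to 30 rests on an assumed share of 0 to 5%. The registry is mainly descriptive, with no primary endpoint and no formal sample size calculation, so no test or power figure is affected. The harm is confined to time-from-index, change-from-baseline and early-safety summaries involving these children. It is worth correcting because it determines what sites record and the correction is nearly free.

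**What to change.** In Sections 1.2 and 9, state that the index date is the actual first DMT dose for every treated child, whatever its calendar date, and that 28 April 2019 limits only how far back charts are abstracted. Word that limit so that it does not cut off the 30-day baseline window of a child who started on or shortly after 28 April 2019. Use the same verb, initiated or received, in both sections.

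Add a derived flag for a first dose before 28 April 2019. For flagged children:

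- measure time from the true first dose, but count follow-up only from when their data begin (delayed entry);
- leave them out of change-from-baseline and early-treatment safety summaries when no pre-treatment baseline is available;
- keep them in utilization counts.

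The cost is about one sentence in each section and one flag. The small downside is that a few children drop out of baseline-anchored summaries.

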### **11.3. Methods of Analysis**

The statistical analysis to assess the primary endpoints will be mostly descriptive. Data quality will be assessed by describing recruitment figures and data completeness (percentages of missing values). Patient characteristics will be displayed in terms of demographic data and disease characteristics at first diagnosis. Time-to-event endpoints will be estimated and displayed using the Kaplan-Meier method. Continuous data will be summarized by arithmetic mean, standard deviation, minimum, 25% quantile, median, 75% quantile, maximum, and the number of complete and missing observations. If appropriate, continuous variables can also be presented in categories. Categorical data will be summarized by the total number of patients in each category and the number of missing values. Relative frequencies are displayed as valid % (number of patients divided by the number of patients with non-missing values). Details on statistical methods and potential subgroup analyses will be included in an SAP.

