### **12.4. Participant Information and Consent**

Prior to any data collection under this protocol, informed consent with the approved ICF must be obtained in accordance with local practice and regulations.

The background of the proposed study, the procedures, the benefits and risks of the study, and that study participation is voluntary for the participant must be explained to the participant (or the participant's legally authorized representative). The participant must be given sufficient time to consider whether to participate in the study.

In addition, participants who have the capacity should provide their assent to participate in the study. The level of information provided to participants should match their level of understanding as determined by the Investigator and in accordance with applicable regulations and guidelines.

A copy of the signed and dated ICF and assent must be given to the participant and/or the participant's legally authorized representative. The original signed and dated ICF will be retained with the study records. Local regulations must be complied with in respect to the final disposition of the original and copies of the signed and dated ICFs.

Confirmation of informed consent and assent must also be documented in the participant's medical record.

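### Counting survival of DMT-treated children from an index date that precedes enrolment, by Kaplan-Meier without delayed entry, would bias treated survival upward; Section 11.3 should rule this out.

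*Protocol*

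**What the plan says.** Section 1.2, Note 2, sets the index date by treatment: "The index date for patients treated with any DMTs will be the date of DMT initiation". For children not on DMT, the same note says that "the index date for those untreated patients will be the date of study enrollment". Section 9 repeats the rule for treated patients: "For the DMTs treated group, the date of patients initiating DMT will be defined as the index date". It does the same for the untreated: "For patients not receiving DMTs, the date of enrollment into the registry will be the index date". Note 1 of Section 1.2 puts pre-enrolment time into the data set: "The study will retrospectively collect available data for patients who initiated DMT prior to recruitment initiation starting from index date". It also sets 28 April 2019 as the earliest index date.

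Enrolment comes later. Section 11.4 schedules the first patient for Q3 2021, and Section 9 gives a 24-month recruitment period. Three rules govern entry:

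- Section 12.4: "Prior to any data collection under this protocol, informed consent with the approved ICF must be obtained".
- Section 6.1: "Age < 18 years at enrollment".
- Section 1.1 (Visit Schedule): enrolment data are taken at a routine clinic visit, and follow-up then runs for up to 60 months.

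Section 4 lists time to mortality among the additional endpoints, under the objective of describing DMT effectiveness. The estimator is in Section 11.3: "Time-to-event endpoints will be estimated and displayed using the Kaplan-Meier method". The protocol does not mention left truncation, delayed entry or a landmark.

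**The concern.** A child who started DMT in 2019 and died in 2020 would not normally reach an enrolment visit in 2021. A child who started on the same day and survived would. If both belong to the population being described and the clock starts at DMT initiation, only the survivor is counted, and is counted as at risk during months in which no death could have been recorded. An ordinary Kaplan-Meier curve treats those months as observed survival.

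Untreated children start at enrolment and carry no such months. If the two curves are shown side by side, part of any gap comes from the two clocks.

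At stake is the credibility of the survival description for DMT in a sponsor-funded registry. Four yearly interim analyses are planned (Section 11.4), and each would repeat the error.

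**Working it through.** The protocol states no survival figure, event count or power, so there is none to reproduce.

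**1. Longest possible gap between index date and enrolment** (days divided by 30.4375)

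- 28 April 2019 to 1 July 2021: 795 days = 26.1 months. To 30 September 2021: 886 days = 29.1 months.
- Adding 24 months of recruitment, to 1 July 2023: 1,525 days = 50.1 months. To 30 September 2023: 1,616 days = 53.1 months.
- Untreated patients: 0 months.

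These are maxima, not typical values.

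**2. What ordinary Kaplan-Meier would estimate**

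Let T be survival from DMT start and L the gap from DMT start to enrolment. Only patients with T > L are enrolled. With 60 months of follow-up after enrolment and ignoring dropout, nobody is censored before month 24. The unadjusted curve at t = 24 therefore estimates

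S_naive(24) = P(T > max(24, L)) / P(T > L).

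For a fixed gap L below 24 this is S(24)/S(L), which is at least S(24). For L of 24 or more it is 1. If the gap is unrelated to prognosis, the bias cannot be negative.

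**3. Size, under stated assumptions**

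Assume a constant hazard λ = −ln S(24)/24. Neither the death rate on DMT nor the gap distribution is in the protocol, so two gap assumptions are used for prior starters.

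*Shorter gaps: L uniform on 0 to 29 months.* For true S(24) = 0.80:

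- λ = 0.009298, 29λ = 0.2696, exp(−29λ) = 0.7637.
- Denominator: (1 − 0.7637)/0.2696 = 0.8765.
- Numerator: (24/29)(0.80) + (0.80 − 0.7637)/0.2696 = 0.7968.
- S_naive = 0.7968/0.8765 = 0.909.

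*Longer gaps: DMT start uniform from 28 April 2019 to 30 June 2021, enrolment uniform over the next 24 months.* The mean gap is about 13 + 12 = 25 months. The same ratio was evaluated by simulation.

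With a share p of enrolled treated patients being prior starters and the rest starting at enrolment, the estimate is p × S_naive + (1 − p) × S(24). For the shorter gaps, S(24) = 0.80 and p = 0.25: 0.25 × 0.909 + 0.75 × 0.80 = 0.827.

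| True 24-month survival | Longer gaps: all / half / quarter prior starters | Shorter gaps: all / half / quarter |
|---|---|---|
| 95% | 99 / 97 / 96% | 98 / 96 / 96% |
| 90% | 98 / 94 / 92% | 96 / 93 / 91% |
| 80% | 96 / 88 / 84% | 91 / 85 / 83% |
| 60% | 91 / 76 / 68% | 80 / 70 / 65% |

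If the share is defined among all who started DMT, including those who died before enrolment, the mixed figures are a little lower. For example, with longer gaps, 60% true survival and a quarter prior starters, the estimate is 65% rather than 68%.

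**4. Effect of delayed entry**

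Letting each patient join the risk set at enrolment brings the simulated 24-month estimate back to the truth within about half a point for the shorter gaps and within about 2 points for the longer gaps.

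**5. Price of delayed entry**

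Under the longer gaps, only 0.7% of patients have a gap under 3 months and 2.9% under 6 months. Even if all 600 planned patients were treated prior starters, that is about 4 and 17 patients (0.007 × 600 = 4.2; 0.029 × 600 = 17.4).

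**The case against.** Four stronger readings are tempting, and the protocol does not support them.

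- *That the protocol counts mortality from DMT start.* No sentence says so. The index date is introduced for data collection and the baseline window, and Section 11.3 gives no time origin. Sections 11.1 and 11.3 leave analysis details to an SAP, which was not available here. A left-truncated Kaplan-Meier would be consistent with Section 11.3 as written, so the point is conditional. What remains is that the protocol fixes unequal index dates, retrospective inclusion and an estimator, defines no other time zero, and does not say how pre-enrolment time is treated. Following those choices literally produces the bias.
- *That deceased children cannot be entered.* This is inferred. Section 6.1 allows a parent or guardian to consent, so consent alone does not prove the child is alive. Section 9 lets retrospective collection close on the last known survival status before recruitment opened, which could be read as admitting chart-only cases. However, that sentence concerns a participating patient and gives no route for enrolling a child who has died. The routine-visit rule in Section 1.1 and the enrolment-age rule in Section 6.1 point the other way. If such cases are admitted, the bias shrinks.
- *That a planned treated-versus-untreated comparison is biased.* No formal survival comparison is specified. Section 4 says effectiveness is to be described, and Section 11.3 calls the analysis mostly descriptive. Only a side-by-side display would be affected.
- *That the main result is at risk.* Mortality is an additional endpoint. The primary objective is natural history and DMT utilization, with primary endpoints marked not applicable.

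It is also fair that the largest figures need every treated patient to be a prior starter and mortality to be high. With 98% true survival the unadjusted estimate under the longer gaps is 99.7% even if all are prior starters.

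**Conclusion.** The point holds conditionally. If time to mortality runs from the index date and ordinary Kaplan-Meier is used, survival of patients who started DMT before enrolment is overstated. Patients who start at or after enrolment are unaffected.

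At 24 months the excess ranges from about 1 point (true survival 95%, a quarter prior starters) to about 30 points (true survival 60%, all prior starters, longer gaps). These sizes rest on an assumed constant hazard, assumed gaps and an assumed share of prior starters. The upward direction does not depend on the death rate or the share. It does require that deceased patients are in practice not entered and that the gap is unrelated to prognosis.

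This should be fixed, though it is not critical: the endpoint is additional and descriptive, and the remedy is cheap.

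**What to change.** **Section 11.3 (and the SAP).** State the time origin of each time-to-event analysis. Where it precedes enrolment, require delayed entry: patients join the risk set at the enrolment or consent date (left-truncated Kaplan-Meier). Show the number at risk over time. Where early risk sets are too small, report survival conditional on reaching a landmark time, chosen by a rule fixed in advance. As a sensitivity analysis, restrict to patients starting DMT at or after enrolment. If treated and untreated curves are displayed together, state that their time origins differ.

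**Section 9.** Say whether the sentence on the last known survival status allows deceased patients to be entered from charts. Reconcile it with the visit rule in Section 1.1, the eligibility rule in Section 6.1 and the consent rule in Section 12.4.

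**Cost.** Wording and one extra date in the survival program; the consent date is already recorded, so no new data are needed. The statistical price is real: early risk sets shrink, and early estimates may be wide and unstable. Delayed entry also assumes that, among those still alive, time of enrolment is unrelated to prognosis; the restricted sensitivity analysis gives some check on this.
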